## Abstract

**Background:**

Prednisone plus azathioprine is considered the mainstay of therapy in the current recommendations for autoimmune hepatitis (AIH). However, it does not provide good benefits for AIH patients because of its serious side effects. Therefore, more and more AIH patients prefer to seek for traditional Chinese medicine (TCM) to manage their symptoms and reduce the side effects of steroids in China. Shu-Gan-Jian-Pi Decoction is a popular used Chinese herbal formula in Guangdong province of China, which has demonstrated the effect of improving efficacy and reducing side effects of corticosteroids in AIH patients. The aim of this study is to evaluate the effects of Shu-Gan-Jian-Pi Decoction combined with steroid in AIH patients. So, this study aims to explore whether the combination treatment of Shu-Gan-Jian-Pi Decoction and steroid standard therapy could improve the clinical management of AIH.

**Methods:**

A prospective non-randomized study on AIH will be conducted between October 2015 and June 2017 in Guangdong Provincial hospital of Chinese medicine. Eligible AIH patients will be classified as the case group (*n* = 66) and the control group (*n* = 66) based on the interventions. Patients taking Shu-Gan-Jian-Pi Decoction combined with prednisone and azathioprine will be in the case group and those taking prednisone and azathioprine will be in the control group. The whole study will last 48 weeks, including a 24-week observation period and a 24-week follow-up period. The primary outcome was complete response to therapy, defined as complete biochemical remission at the patient’s last visit of observation period and the absence of predefined steroid-specific side effects throughout treatment.

**Discussion:**

This trial will evaluate the efficacy and safety of Shu-Gan-Jian-Pi Decoction combined with prednisone and azathioprine on AIH patients. The achievement of this trial will provide evidence-based data for Shu-Gan-Jian-Pi Decoction, which could provide good benefits for AIH patients.

**Trial registration:**

Chinese Clinical Trial Registry: ChiCTR-OOC-15006155.

Registration date: 28 March 2015

## Background

Autoimmune hepatitis (AIH) is characterized by acute or chronic liver inflammation, which is considered to be associated with autoimmune response in liver cells. Previous studies [1] have proved that AIH can easily progress to cirrhosis or liver failure, and even some patients need for liver transplantation finally. It is reported that 40% of untreated severe AIH patients might die within 6 months, and those surviving commonly develop cirrhosis and subsequent complications of portal hypertension [2]. Moreover, it accounts for 2.6% of the transplantations in Europe [3] and 5.9% in the United States [4]. Due to this poor prognosis and the increasing detection rate, more and more studies focus on the management of AIH recently. It is well known that low dose prednisone plus azathioprine is the standard therapy for AIH, with alleviation of symptoms achieved in 60 to 80% of cases [5]. However, it must be noted that 50 to 86% of patients witness a recurrence of the disease after stopping medications, while 13% of patients stop the treatment too early due to the severity of the side effects and 9% of patients’ situation will deteriorate, even though they are administered medications according to guidelines [6]. Due to the high recurrence rate and the common side effects of corticosteroids, more and more AIH patients seek for traditional Chinese medicine (TCM) to manage their symptoms and reduce the side effects of corticosteroids in China.

In recent years, more and more researchers try to explore the efficacy and safety of combination treatment of steroids and Chinese herbal medicine in AIH patients. Fortunately, a number of clinical studies have proved the positive efficacy of TCM in Chinese AIH patients [7–9], such as alleviating liver inflammation; reducing side effects of corticosteroids and improving TCM signs and symptoms. But most of these studies were case reports or expert experience, or did not report strict inclusion and exclusion criteria, or had small sample size. Moreover, even the formulation of TCM was in the form of capsule or injection in some of these trials. Thus, current studies do not provide sufficient evidence to support the effectiveness of TCM in the treatment of AIH. So we have made a further research on the issue to explore whether the combination treatment of TCM and steroid standard therapy could improve the clinical management of AIH. Shu-Gan-Jian-Pi (SGJP) Decoction, made by famous traditional Chinese medicine doctor [name], is a popular used Chinese herbal formula in Guangdong province of China, which has demonstrated the effect of improving efficacy and reducing side effects of corticosteroids in AIH patients. This recipe, coming from the Golden mirror of medicine (a famous textbook of TCM), is widely used in treating chronic liver disease patients with pattern of live stagnation and spleen deficiency for more than 30 years. The results of previous clinical studies and animal experiments [10, 11] of SGJP Decoction provide the evidence that it has the effects of immunomodulatory and anti-liver-inflammation. However, previous clinical studies were retrospective study or focus on the patients with autoimmune diseases combined with hepatitis B, not on the AIH itself. Therefore, we conduct a prospective study to evaluate the efficacy and safety of SGJP Decoction combined with steroid standard therapy in AIH patients.

## Methods/design

### Study design

This is a prospective, non-randomized, controlled study. One-hundred and thirty two AIH patients visited in Guangdong provincial hospital of Chinese medicine at the first time will be enrolled and divided into two groups with a case: control ratio of approximately 1:1. While patients in the control group received the steroid standard therapy, patients in the case group are treated with combination treatment of SGJP decoction and the steroid therapy. Both of the treatment and follow-up period will be for 24 weeks. The details of the flow chart of this trial are shown in Fig. 1.

**Fig. 1 Fig1:**
[figure not shown]
Flow chart of the current trial. PRED: Prednisone; AZA: azathioprine; SGJPD: Shu-Gan-Jian-Pi Decoction

### Patient population

A total of 132 AIH patients, who fulfill the screening criteria, is being enrolled and followed up between October 2015 and June 2017. According to the patients’ preference, the eligible AIH patients will be divided into two groups: the case group (to receive SGJP Decoction combined with low dose prednisone and azathioprine, *n* = 66) or a control group (to receive low dose prednisone and azathioprine, *n* = 66).

### Diagnostic criteria

The patients’ western medicine diagnostic criteria are based on AIH guideline which was established by American Association for the Study of Liver Diseases (AASLD) [12]. The TCM diagnosis of AIH patients is based on “Clinic terminology of traditional Chinese medicine medical diagnosis and treatment-Syndromes [13]”.

### Inclusion criteria

(1) All the patients had either a first diagnosis of AIH or were experiencing relapse after a previous diagnosis of AIH based on histology findings within 12 months before screening. (2) TCM syndrome type: liver stagnation and spleen deficiency. (3) Patients fulfill indications for treatment: serum aspartate aminotransferase (AST) ≥ 10-fold upper limit of normal (ULN) levels; or Serum AST ≥ 5-fold ULN and gammaglobulins ≥ twice ULN; or Bridging necrosis or multiacinar necrosis on histopathological examination (4) aged from 18 to 65 years.

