#### Sample size and statistical methods

This prospective study is intended to evaluate the efficacy and safety of the combination treatment of SGJP Decoction and steroid standard therapy on AIH. Since there is still no enough reliable data to accurately calculate the sample size for our study, 20 hepatology experts in Chinese medicine or integrative medicine with more than 20 years clinical experience were asked for advice. After two rounds of meetings with these experts, we agreed that 110 patients should be sufficient to gather enough information in order to plan such a clinical trial. And 132 cases are needed if there is a dropout rate of 15%.

The statistical analysis for this study will be performed using SPSS software version 19.0 (SPSS Inc., Chicago, IL, USA). Data will be presented as mean and standard deviation, or frequency and percentages. Comparisons will be conducted between the case group and the control group, also between pre-treatment and post-treatment in each group. For normally distributed variables, means will be compared by using t-tests (two-tailed), and nonparametric variables will be analyzed using Pearson chi-squared tests or Fisher exact tests. All *P*-values will be two-tailed. A P-value of less than 0.05 will be considered statistically significant.

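### Relapse status may confound the preference-based comparison, and the methods section fixes an unadjusted test while the propensity scores appear only in the Discussion

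*Protocol article*

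**What the plan says.** All of these points come from the protocol article.

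- **Inclusion criteria.** Patients may have "either a first diagnosis of AIH or were experiencing relapse after a previous diagnosis of AIH". No share or cap is set for either kind.
- **Patient population.** Groups are not randomized: by patient "preference, the eligible AIH patients will be divided into two groups", 66 in each.
- **Background.** "Due to the high recurrence rate and the common side effects of corticosteroids, more and more AIH patients seek for traditional Chinese medicine". The same section reports that "50 to 86% of patients witness a recurrence of the disease after stopping medications".
- **Sample size and statistical methods.** "Comparisons will be conducted between the case group and the control group", using t-tests for normally distributed variables and Pearson chi-squared or Fisher exact tests otherwise, two-sided at 0.05. No covariate or stratum is mentioned.
- **Discussion.** The lack of randomization is listed as the first limitation, and propensity scores are offered as the remedy. No covariates are named, and the methods section does not mention the method.

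**The concern.** Disease history is a yes/no fact known at screening, because eligibility depends on it. A relapsing patient has lived through one of the reasons that the Background gives for seeking Chinese medicine. Such a patient may also have had steroids before, which bears on the second reason, side effects. When preference decides the group, it is plausible that the two groups contain different proportions of relapse patients.

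Disease history may also bear on the primary outcome. Complete response requires normal aminotransferases and IgG together with freedom from steroid-specific side effects, and earlier disease and treatment could affect either part. If both links hold, the unadjusted difference in complete response combines the effect of the decoction with the difference in case mix. A chi-squared or Fisher test cannot separate them. The distortion could hide a real benefit or create an apparent one.

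**Working it through.** **The article's own figures.** The base figure is expert consensus: "we agreed that 110 patients should be sufficient to gather enough information in order to plan such a clinical trial". It has no response rate, effect size or power behind it, so it cannot be re-derived. The article then says that "132 cases are needed if there is a dropout rate of 15" per cent. The usual inflation gives 110 / (1 - 0.15) = 129.4, so 130, which is within two patients of 132. At 132 enrolled, 132 x 0.85 = 112.2 are retained. The stated sample size is not at issue here. It only supplies the group sizes below: 110 / 2 = 55 evaluable and 132 / 2 = 66 enrolled per group.

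**Inputs that the article does not give.** It reports neither the relapse share in each group nor the response rate by disease history. All such values below are assumptions.

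**Bias formula.** With no decoction effect, the expected unadjusted difference (case minus control) is

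(relapse share in case group - relapse share in control group) x (response in relapse - response in first diagnosis).

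**Rejection rate.** Let a and b be the resulting response rates in the case and control groups, D = |a - b| and p = (a + b) / 2. The standard error under the null is SE0 = sqrt(2p(1 - p) / n). Under the actual rates it is SE1 = sqrt([a(1 - a) + b(1 - b)] / n). The two-sided rate is Φ((D - 1.96 SE0) / SE1) + Φ((-D - 1.96 SE0) / SE1).

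**One case in full.** Take relapse shares of 60% and 30%, with response 60% in first diagnosis and 30% in relapse.

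- Case group: a = 0.6 x 0.3 + 0.4 x 0.6 = 0.42.
- Control group: b = 0.3 x 0.3 + 0.7 x 0.6 = 0.51.
- Difference: 0.42 - 0.51 = -0.09, which equals 0.3 x (-0.3).
- At n = 55, SE0 = 0.0951 and SE1 = 0.0947. The rate is Φ(-1.02) + Φ(-2.92), or about 0.156.

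**Results at 55 per group, no decoction effect:**

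| Relapse share, case vs control | Response, first diagnosis vs relapse | Spurious difference (points) | Two-sided error |
|---|---|---|---|
| 30% vs 30% | 60% vs 30% | 0 | 5.0% |
| 60% vs 30% | 50% vs 50% | 0 | 5.0% |
| 50% vs 30% | 50% vs 30% | -4 | 7.1% |
| 60% vs 30% | 60% vs 30% | -9 | 15.6% |
| 70% vs 20% | 60% vs 30% | -15 | 34.9% |
| 60% vs 30% | 40% vs 60% | +6 | 9.6% |
| 70% vs 20% | 40% vs 60% | +10 | 18.1% |

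At 66 per group the -15 point row gives 40.7%. A larger sample does not help, because the bias stays and the standard error shrinks.

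**With a real effect.** Suppose a true benefit of 15 points, the same in both kinds of patient. A bias of -6 would show it as 15 - 6 = 9 points, and a bias of +6 as 15 + 6 = 21 points.

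**Scope of these figures.** They describe the unadjusted comparison only. If relapse status is balanced exactly, or the analysis is stratified on it, this component is zero. Confounding by other factors is a separate matter.

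**The case against.** The strongest reply is that confounding is already acknowledged: the Discussion commits to propensity scores, a binary baseline factor is easy to balance and to check, and the covariate list belongs in an analysis plan that is not shown. Much of this stands. An unlisted covariate would not be a finding on its own, and none of the figures above measures bias left after a propensity analysis. What the reply does not remove is a disagreement inside the article. The methods section fixes unadjusted tests, the Discussion promises adjustment, and nothing says which is primary.

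Two stronger readings are tempting and should be resisted.

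- A reader might infer that the groups *will* differ in relapse share. The Background speaks of AIH patients in general, names steroid side effects alongside recurrence, and does not compare relapsed with newly diagnosed patients. A new patient who is told of the recurrence rate has a similar motive. The text supports no more than that the shares may well differ.
- A reader might infer that the article predicts the direction, so that a useful decoction would look ineffective. It says nothing on whether relapse patients reach complete response more or less often. Recurrence after stopping medication is not the same as treatment failure. The bias could favour the decoction, oppose it or be absent.

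Nor does it settle the matter that the Study design section describes patients visiting this hospital for the first time. A first visit there does not exclude relapse, and the inclusion criteria admit it.

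**Conclusion.** The concern holds in a limited form. Disease history is a plausible confounder in a comparison formed by preference. The analysis fixed in the methods section does not handle it, and the analysis that could handle it appears only in the Discussion.

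Bias requires two things that the article neither states nor excludes: unequal relapse shares, and a link between relapse status and complete response. Its size and sign therefore cannot be fixed from the document. Over the assumed inputs it runs from -15 to +10 points. The milder scenarios give about -4 to +6, and it is zero if either condition fails. The uncertainty about direction is itself a reason to settle the adjustment in advance, since it could not be corrected for afterwards by argument. The point deserves a change but is not fatal to the study.

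**What to change.** In the statistical methods section, replace the unadjusted primary test with the propensity-score analysis promised in the Discussion. Name first diagnosis versus relapse as a required covariate, balanced exactly or used as a stratum, alongside the other baseline confounders in a single model. Report the adjusted risk difference in complete response with its 95% confidence interval, and show the balance achieved on disease history. Results within each kind of patient may be shown descriptively only, because about 110 patients split in two will be imprecise.

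Two simpler routes are less good. A Mantel-Haenszel difference stratified on relapse alone would leave every other preference-related confounder unadjusted. Separate propensity models in each stratum would be thin at this sample size.

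The change needs no new data, visits or patients, since disease history is already established for eligibility. The article describes the trial as recruiting, so at that stage the change can still be specified in advance. The cost is slightly more analysis work and some loss of precision.

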### Exclusion criteria

(1) co-infection with hepatitis virus or human immunodeficiency virus; (2) evidence of advanced liver diseases, such as decompensated cirrhosis, severe hepatitis, or hepatic carcinoma; (3) evidence of serious uncontrollable diseases, such as heart, brain, kidney or gastrointestinal primary disease, etc.; (4) recent treatment with drugs with known liver toxicity; (5) pregnancy or lactation; (6) parenteral administration of blood or blood products within 6 months before screening.

### Interventions

While patients in the control group received the steroid standard therapy, patients in the case group are treated with combination treatment of SGJP decoction and the steroid therapy. The primary and secondary outcomes are assessed and analyzed after 24-week treatment.

### Steroid standard therapy

The steroid standard therapy, recommended by the AASLD AIH Guidelines [12], was as follows: prednisone (starting dose 30 mg/day, tapered to 10 mg/day) plus Azathioprine (administered at a dose of 50 mg/day). More details are shown in Fig. 1. According to the changes of patients’ conditions, doctors could adjust the specific agents and the doses, but the groups are not allowed to be changed until week 24.

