### Outcome measurements

#### Primary outcome

The primary outcome was complete response to therapy, defined as complete biochemical remission at the patient’s last visit of observation period and the absence of predefined steroid-specific side effects throughout observation period (moon face, central obesity, buffalo hump, diabetes and increased intraocular pressure, etc.). Biochemical remission was defined as complete normalization of aminotransferase levels including IgG.

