#### Secondary outcomes

Secondary outcomes include the proportion of patients whose g-glutamyl transpeptidase (GGT) and total bilirubin (TBIL) levels decrease more than 50% after 4-week treatment as well as the GGT and TBIL normalization rate, the remission rate of patients’ clinical symptoms and the occurrence rate of the immunosuppressive agents’ side effects after 24-week treatment.

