#### Safety outcomes

The results of a routine blood test, routine urine test, routine stool test, renal function test and electrocardiogram are assessed before and after the treatment to ensure the safety of this study. Further more, a urine pregnancy test or serum human chorionic gonadotropin test must be done before enrolling a women patient of childbearing age.

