## Conclusions

This prospective study will verify that SGJP Decoction could reduce steroid dosing and side effects of steroid. On one hand, it will give evidence data for SGJP on AIH so that it could be applied widely and bring more good benefits for AIH patients. On the other hand, the findings will provide a basis and a new direction for further confirmatory studies.

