### Trial status

This trial is currently recruiting participants.

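### The Conclusions promise to verify a reduction in steroid dosing, but no listed outcome measures steroid dose

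*Protocol article*

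**What the plan says.** Four parts of the protocol article bear on this point.

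- **Background treatment (Steroid standard therapy).** Both groups receive "prednisone (starting dose 30 mg/day, tapered to 10 mg/day) plus Azathioprine (administered at a dose of 50 mg/day", with further detail referred to Fig. 1, which is not shown. As the patient's condition changes, "doctors could adjust the specific agents and the doses, but the groups are not allowed to be changed until week 24".
- **Allocation (Patient population).** By the patients' "preference, the eligible AIH patients will be divided into two groups". The article describes no blinding and no placebo decoction.
- **Outcomes (Outcome measurements).** The primary outcome combines biochemical remission at the last visit of the observation period with "the absence of predefined steroid-specific side effects throughout observation period". The secondary outcomes are GGT and TBIL measures, remission of symptoms, and side effects of the immunosuppressive drugs. The safety outcomes are laboratory tests and an electrocardiogram.
- **Stated conclusion (Conclusions).** "This prospective study will verify that SGJP Decoction could reduce steroid dosing and side effects of steroid".

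**The concern.** The closing sentence makes two claims: less steroid, and fewer steroid side effects. A reader who looks for the result that would carry each claim finds outcomes for the second and none for the first. This matters because dose is left to the doctor. Had the protocol fixed an identical dose for everyone, a dosing conclusion would be impossible by design. As it stands, dose can differ between patients and groups, so the question can be asked, but no declared outcome answers it.

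At stake is a statement on steroid sparing, a clinically attractive claim in this disease, made with no prespecified measure, time point or group comparison behind it. If the investigators chose a dose measure after seeing the data, the claim would rest on a selection the reader could not check.

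**Working it through.** The plan gives no figure on this point to reproduce. The check sets the listed outcomes against the two halves of the conclusion.

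**Step 1: count the listed measures.**

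| Section | Measures | Number | Steroid dose or change of agent |
|---|---|---|---|
| Primary outcome | complete response | 1 | 0 |
| Secondary outcomes | GGT fall over 50% at week 4; TBIL fall over 50% at week 4; GGT normalisation; TBIL normalisation; symptom remission; immunosuppressant side effects | 6 | 0 |
| Safety outcomes | blood, urine, stool, renal function, electrocardiogram | 5 | 0 |
| Total | 1 + 6 + 5 | 12 | 0 |

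The pregnancy test is done before enrolment and is not counted. The total depends a little on whether GGT and TBIL are split, and the five safety tests were never likely to include a dose measure. The zero does not depend on either choice: it is 0 of 7 for efficacy and side effects alone, and 0 of 12 overall.

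**Step 2: match each half of the conclusion to an outcome.**

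- Side effects of steroid: covered by the second component of the primary outcome and by the last secondary outcome.
- Steroid dosing: no outcome.

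**Step 3: is dose fixed by the design?** No. Steroid standard therapy gives a starting dose, a tapered dose and an azathioprine dose, then lets doctors change agents and doses. Only group membership is held until week 24.

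**Step 4: illustrate what a dose outcome would capture.** From the document: 30 mg/day tapered to 10 mg/day, and 24 weeks = 168 days. Assumptions: a straight-line taper (mean 20 mg/day while tapering), then 10 mg/day, with taper lengths of 4, 12 and 24 weeks.

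Cumulative dose = taper days × 20 + remaining days × 10.

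- 4 weeks: 28 × 20 + 140 × 10 = 560 + 1,400 = 1,960 mg
- 12 weeks: 84 × 20 + 84 × 10 = 1,680 + 840 = 2,520 mg
- 24 weeks: 168 × 20 = 3,360 mg

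Each additional taper week adds 7 × (20 − 10) = 70 mg. The longest of these tapers gives 3,360 / 1,960 = 1.7 times the exposure of the shortest, with the same starting and final dose. These are not limits, because doctors may leave the dose range and Fig. 1 may set a schedule. They are not an estimate of any difference between the groups.

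**The case against.** The strongest reply is that dosing as an expected result appears in one closing sentence only. The aims in the abstract, the Background, the sample size section and the Discussion concern efficacy, safety and clinical management, and the listed outcomes fit those aims. The Conclusions also look ahead to later confirmatory studies, and the Discussion admits that the sample is small. On this view the sentence overclaims, while the outcome set does not fail its objective. That stands in part: it is why deleting the dosing claim is an acceptable remedy. It does not remove the mismatch, because the sentence says what the study will verify.

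A second reply is that doses may be recorded on case report forms and tabulated under the full protocol or analysis plan, and that Fig. 1 may give the taper. This also stands, and nothing here says that doses are unrecorded or that a schedule is absent. But a taper schedule is not an outcome, and a recorded dose that is not declared as an outcome still leaves the dosing conclusion without a declared result.

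A reader might go further and infer that flexible prescribing biases complete response in favour of the decoction. The documents do not support that. Adjustment is tied to the patient's condition, which is ordinary care. The two components of the primary outcome also pull in different directions: more steroid tends to favour remission, and less tends to favour freedom from steroid side effects. Neither the direction nor the size of any bias can be derived. Reporting background treatment by group is, moreover, commonly left to documents that are not shown.

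**Conclusion.** The point holds for the dosing half of the conclusion and no further. The article says the study will verify a reduction in steroid dosing, allows dose to vary, and lists 0 dose measures among 12 outcomes. This rests on the outcome sections as printed and on no assumption about Fig. 1 or the full protocol. The cumulative doses above are illustrative and rest on an assumed taper shape and assumed taper lengths.

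Even with dose listed as an outcome, attribution would stay limited. Groups follow patient preference, and since no blinding is described doctors very probably know who takes the decoction. A lower dose in the case group could reflect the decoction, the prescriber's expectation or the kind of patient who chose it. The change is worth making because it is cheap and lets the study report on a claim it already makes, not because the primary result has been shown to be unsound.

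**What to change.** **Preferred.** Under Secondary outcomes, add, by group, the cumulative prednisone dose to week 24, together with any change of immunosuppressive agent, its date and its reason. Take these from prescribing records, report them beside the primary result, and describe a lower dose in the case group as what was prescribed.

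**Otherwise.** Delete the reference to steroid dosing from the Conclusions and keep the side-effect claim, which has outcomes behind it.

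**Cost.** The preferred change needs two recorded items and one table by group. It needs no extra patients, no extra visits and no change of treatment. The article reports that "This trial is currently recruiting participants", so the items must be retrieved from records for patients already enrolled, and the outcome must be labelled as added during recruitment. The deletion costs nothing, but it gives up the steroid-sparing question.
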